### Statistical analyses

To assess whether the randomisation results in two comparable groups at baseline, and whether differential loss to follow-up later occurs, we will use t-tests, chi-square tests and logistic regression (p < .10). Analyses with regard to effectiveness will be based on the intention-to-treat principle.

Missing data at t1 and t2 will be imputed using the expectation-maximisation (EM) method, as implemented in SPSS Missing Value Analysis. It imputes missing values by maximum likelihood estimation using the observed data in an iterative process [44]. All randomised participants will be included in the analyses in line with their allocation, regardless of how many sessions they complete (intention-to-treat principle).

Since the online GOJD is a group course, some subjects will be participating in the same course group, leading to some amount of clustering. The clustering would violate the assumption of independence of observations and might thus affect standard errors and *P*-values. We will therefore use linear regression models, controlling for data clustering, in analysing post-test (t1) between-group differences on the continuous outcome measures. Robust standard errors and correct *P-*values will be obtained using the first-order Taylor-series linearisation method, as implemented in Stata.

Magnitudes of intervention effects will be estimated using Cohen's *d *[45]. Effect sizes will first be calculated for each condition separately by subtracting the mean post-test score from the mean pre-test score and dividing the result by the standard deviation at pre-test. The effect size of the comparison group will then be subtracted from that of the experimental group. A difference in *d *0.5 would indicate that the experimental group mean is half a standard deviation greater than the control group mean. For Cohen's *d*, an effect size of 0.2 to 0.3 may be regarded as a small effect, around 0.5 as a medium effect and 0.8 to infinity as a large effect.

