To determine effect maintenance at 6 months in the experimental group, we will use the follow-up (t2) assessment data. The number of participants showing reliable, clinically significant change on the CES-D from pre-intervention to post-intervention and follow-up will be calculated using the method of Jacobson and Truax [46]. To find predictors for more or less successful intervention outcomes, we will use regression analyses to study effect modification. The individual standardised change scores (effectsizes; pre- to post-intervention) will serve as the outcome measure, and interaction terms between the treatment dummy and participants' characteristics will be included as predictors, along with their constituent main effects. Predictors for successful and unsuccessful outcomes will be demographic variables such as age, gender and educational attainment and course-related variables such as web-chatting experience and motivation to take part in preventive group interventions [43].

To detect possible dose-response relationships in respondents randomised to the course, we will use a linear model to regress the primary outcome (depressive symptoms) on the number of sessions they attended. Tests will be conducted at alpha = .05 with 95% confidence intervals.

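### The effect-modification regressions treat singly EM-imputed t1 scores as observed, so interactions are either shrunk or given too small a standard error, depending on an unstated imputation model

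*Protocol article*

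**What the plan says.** Three statements in the Statistical analyses section of the Protocol article combine here.

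- Imputation: "Missing data at t1 and t2 will be imputed using the expectation-maximisation (EM) method, as implemented in SPSS Missing Value Analysis". The method is described in one further sentence: "It imputes missing values by maximum likelihood estimation using the observed data in an iterative process". The variables in the EM model are not listed, and no correction of standard errors for imputation is described.
- Analysis set: "All randomised participants will be included in the analyses in line with their allocation, regardless of how many sessions they complete".
- Predictor analysis: "The individual standardised change scores (effectsizes; pre- to post-intervention) will serve as the outcome measure, and interaction terms between the treatment dummy". The other half of each interaction is a baseline characteristic, and both main effects stay in the model.

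The test level follows at the end of the section: "Tests will be conducted at alpha = .05 with 95% confidence intervals". The predictor analysis is not exempted from imputation. The robust standard errors in the same section address clustering by course group in the t1 between-group comparison, not imputation. The candidate predictors named include age, gender, educational attainment, web-chatting experience and motivation.

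**The concern.** For a participant without a t1 score, the change score is whatever the EM model implies, yet the regression counts it as an observation. An interaction analysis is sensitive to this in a particular way, because the imputed change either carries the interaction or does not.

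- **EM leaves out the treatment-by-characteristic term.** This covers EM pooled over arms with main effects or outcomes only, and EM run by arm without the characteristic. The imputed changes then contain no interaction and dilute the one in the observed data.
- **EM carries the term.** This covers EM with the product term, or run by arm with the characteristic. The imputed changes then repeat the interaction fitted to the responders and are counted as further evidence for it.

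Finding predictors of better outcome is a named secondary aim. At stake are the size of any reported effect modification under the first reading and the false-positive rate under the second. A reader of the results could not tell which had occurred.

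**Working it through.** **Inputs.** From the article: 121 per arm (Sample size) and a 5% test level (Statistical analyses), taken as two-sided for the interactions. Assumed, because the article gives no figure: the fraction *m* of t1 scores missing (10 to 40%), missingness completely at random, and a t0–t1 correlation of 0.5 (0.3 to 0.7 as a range). EM is read as filling the conditional mean.

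**1. The plan's own figure.** For d = 0.32, one-sided 5%, 80% power: n per arm = 2 × (1.645 + 0.842)² / 0.32² = 120.8, so 121 per arm and 242 in total. The Sample size section's figure reproduces. It powers the main comparison only and enters below simply as the group size.

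**2. EM without the interaction.** For a binary characteristic the interaction δ is a difference of differences among four cell means of change. Each cell mean is (1 − *m*) × observed mean + *m* × imputed mean. The observed part contributes δ and the imputed part contributes 0, so the expected estimate is (1 − *m*) × δ. With δ = 0.50 SD: 0.9 × 0.50 = 0.45; 0.8 × 0.50 = 0.40; 0.7 × 0.50 = 0.35; 0.6 × 0.50 = 0.30.

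**3. EM with the interaction.** The true variance of the estimate is proportional to σ² / [n(1 − *m*)], since only responders inform it. If imputed values had no scatter, the analysis would use a residual variance of (1 − *m*)σ² and divide by n. The ratio of reported to true standard error is then √[(1 − *m*) × (1 − *m*)] = 1 − *m*. The type I error is therefore at most about 2Φ(−1.96(1 − *m*)). This is an upper limit because baseline is not a covariate in the change-score regression, so imputed changes still scatter with t0.

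**4. Simulation.** 121 per arm, binary characteristic at 50% prevalence, correlation 0.5:

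| Missing at t1 (assumed) | EM without the term: estimate of a true 0.50 | EM with the term: false positives | Upper limit from step 3 |
|---|---|---|---|
| 10% | about 0.45 | about 7–8% | 7.8% |
| 20% | about 0.40 | about 9–10% | 11.7% |
| 30% | about 0.35 | about 13–14% | 17.0% |
| 40% | about 0.30 | about 19% | 24.0% |

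**5. Sensitivity.** A separate simulation used a continuous standardised characteristic and correlations of 0.3, 0.5 and 0.7.

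- Without the term, the ratio of estimate to truth was 0.79–0.81, 0.68–0.70 and 0.57–0.60 at 20, 30 and 40% missing. Type I error was 3.5–5.7%.
- With the term, the ratio was 0.97–1.02. Type I error was 8.7–12.0%, 11.1–16.6% and 14.8–21.1%. Heteroscedasticity-robust standard errors did not repair this (9.3–22.5%).
- Complete cases on the same data gave ratios of 0.98–1.02 and type I error of 4.7–6.0%, so the distortions come from the imputation.
- With t2 observed for half of those missing t1 and used in EM (30% missing, correlation 0.5), the ratio without the term was 0.73 and the type I error with it was 13.1%.
- Adding a random residual to each single imputed value did not rescue the plan. False positives were still 9, 11 and 14% with the term, and a true 0.50 was still estimated as 0.39, 0.35 and 0.28 without it.

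**The case against.** **Power.** A reader might infer that the plan will miss real predictors. The figures do not support this. At 30% missing and a true interaction of 0.50 SD, observed change scores gave 36% power and EM-filled change scores (without the term) 32%. With baseline CES-D in the model, both gave 47%. A second run gave 34% against 31%, and 43% against 44%. Setting 47% against 32% would mix two changes, and nearly all of that gap is baseline adjustment, which is a separate matter. Under the first reading the estimate and its standard error shrink together, so the harm is a diluted estimate and not lost detection.

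**False predictors.** A reader might equally infer that the trial will report false predictors. That holds only if EM carries the arm-by-characteristic structure, which the article neither states nor excludes.

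**Missing detail.** The EM variable list is something an article may leave to a fuller document. That stands as far as the list goes. But single imputation, with all randomised participants analysed, is a stated choice, and every EM specification tried produced one of the two distortions.

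**Dropout.** The rate is unknown. The attrition remark in the Background concerns earlier pre-post studies, and the Assessments section plans two reminders and payments. This limits the claim about size but does not remove the mechanism.

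**Overlap.** The root is the single-imputation decision, and changing it generally would also settle this point. The dilution of an interaction is nevertheless specific to these models.

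**Conclusion.** The point stands as a modest, conditional one about a secondary analysis. As written, the predictor regressions give either an interaction shrunk by roughly the missing fraction with a near-nominal test, or an unbiased interaction with an understated standard error. Which one applies depends on an imputation model that the article does not state.

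The size depends on the assumed missing rate. At 10% missing it is small: 0.45 for a true 0.50, or 7–8% false positives. At 30–40% it is material. Shrinkage by exactly the missing fraction requires scores missing completely at random and no informative t2 data; with t2 used in EM it is slightly less. The simulations ignore clustering by course group. The sample size is not affected.

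**What to change.** For the predictor analysis, replace single EM by multiple imputation. Do it separately by arm, or with the arm-by-characteristic terms in the imputation model. Include baseline CES-D and all tested characteristics, and pool with Rubin's rules. This keeps all randomised participants, as the section intends.

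Alternatively, fit the interaction models to participants with an observed t1 CES-D, with baseline CES-D and the main effects in the model. This is valid if missingness depends only on variables in the model.

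In simulation at 10–40% missing completely at random, both options estimated a true 0.50 as 0.49–0.50, with 4–6% false positives.

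Either change costs a sentence or two in the analysis section and needs no new data. The small downside of the second is that it reports fewer participants than were randomised.

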**Methods:**

We will conduct a randomised controlled trial (RCT) in which 244 young people aged 16-25 are randomly allocated to the Grip op Je Dip (GOJD) online group course or to a waiting list control group. The participants will be recruited from the general population. The primary outcome measure will be the severity of depressive symptoms according to the Center for Epidemiological Studies Depression Scale (CES-D). Other outcomes will include anxiety (Hospital Anxiety and Depression Scale-Anxiety, HADS) and mastery (Mastery Scale). Assessments will take place in both groups at baseline and three months later. Effect maintenance will be studied in the GOJD group six months after baseline, with missing data imputed using the expectation-maximisation method. Mediators and predictors of better outcomes will also be identified.

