### Sample

The sample is to consist of 242 young people aged 16-25 with mild to moderate depressive symptoms. The inclusion criteria are as follow: age 16 to 25, informed consent (including parental consent if aged 16 or 17) and a CES-D depression score from 10 to 45. The CES-D cut-off score for clinical depression is 16 [31] for adults, and for adolescents it is either 22 [32] or 24 [33]. For subclinical depression, no CES-D cut-off scores have been determined, but we have set the lower limit at 10 for this study. Applicants will be excluded if there are indications of suicidal ideation with intent and plan as assessed with the MINI-International Neuropsychiatric Interview (MINI-Plus) [34,35]. MINI-Plus assessment is mandatory for individuals with CES-D scores higher than 24; the MINI-Plus will be administered online in the chatroom.

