### Assessments

Assessments will take place before randomisation (t0), three months later (t1) and three months after t1 (t2). Participants in both groups will receive automated emails with invitations to complete online questionnaires. Subsequent email reminders will be sent five and ten days after the first invitation, if necessary. To encourage response, participants will receive 10 euros' compensation for completing the t1 questionnaire and 10 euros for the t2 questionnaire. If they complete both questionnaires, a 5-euro bonus will be added, totalling 25 euros.

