#### Additional measures

##### Motivation

At baseline we will assess motivation to take part in preventive group interventions, using four subscales of the Nijmegen Motivation List for Prevention (NML-P) [43]. The subscales are Readiness, Doubt, Support and Burden. Their reliability is acceptable, with Cronbach's alphas ranging from .80 to .84.

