#### Other information

At baseline we will also assess demographic information and any previous or present receipt of professional help for psychological problems. Follow-up assessments will record the use of professional help (t1 and t2) and participants' evaluations of the intervention (t1, in course group only).

Course adherence will be measured in terms of session attendance and completion of homework assignments. Session attendance will automatically be recorded when the participant enters the chatroom. Homework completion will be recorded by the facilitators in an online logbook.

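### The exploratory dose-response model names sessions attended as its only regressor, so its slope is confounded if baseline severity or motivation influences attendance

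*Protocol article*

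**What the plan says.** The last paragraph of Statistical analyses in the Protocol article gives the purpose and population as "To detect possible dose-response relationships in respondents randomised to the course" and the model as "we will use a linear model to regress the primary outcome (depressive symptoms) on the number of sessions they attended". The test level follows: "Tests will be conducted at alpha = .05 with 95% confidence intervals". The sentence gives neither a time point for the outcome nor any covariate.

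Other sections show what is available for adjustment. Baseline CES-D is measured before randomisation, and entry requires "a CES-D depression score from 10 to 45". Under Motivation: "At baseline we will assess motivation to take part in preventive group interventions". Under Other information: "Session attendance will automatically be recorded when the participant enters the chatroom".

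Statistical analyses specifies cluster-robust standard errors for the between-group comparison at t1. It does not say whether they also apply to this within-arm model.

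**The concern.** The comparison is between people in one arm who attended many sessions and people in the same arm who attended few. Randomisation does not balance those groups. Severity at entry covers a wide range and is a stratification factor, so it is reasonable to expect it to predict later CES-D. Motivation is listed in the same section as a candidate predictor of outcome and could plausibly also influence attendance.

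If either factor is related to both attendance and later symptoms, the coefficient for sessions includes that relation. A slope could then be read as evidence that each session reduces symptoms when it partly reflects who kept attending. If instead the more depressed participants attend more, the same mechanism would hide a real benefit. What is at stake is the interpretation of one secondary result.

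**Working it through.** **Plan's own figure.** The arm size used below is the plan's. With d = 0.32, one-sided alpha .05 and 80% power, n per arm = 2 × (1.645 + 0.842)² / 0.32² ≈ 12.37 / 0.1024 ≈ 120.8. This rounds up to 121 per arm and 242 in total, as stated under Sample size.

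**Inputs.** From the article: 121 participants in the course arm, 0 to 6 sessions, alpha .05 (taken as two-sided, because the sentence does not say), and CES-D level as the outcome. Assumed, because the article gives neither: the correlation q between baseline CES-D and the tendency to attend, and the correlation ρ between baseline and follow-up CES-D. Follow-up is taken to be t1. Attendance is spread evenly over 0 to 6 sessions, outcomes are complete, and there is no clustering. The true effect of sessions is zero.

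**Expected bias.** With no session effect, the correlation between sessions and follow-up CES-D is roughly ρ × q. For ρ = 0.5 and q = -0.3 this is -0.15. The simulation gives -0.145, slightly smaller because attendance is cut into whole sessions.

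**False-positive rate of the model as written** (10,000 replicates per cell, least squares, two-sided .05):

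| ρ (t0-t1) | q = 0 | q = -0.1 | q = -0.2 | q = -0.3 | q = -0.5 |
|---|---|---|---|---|---|
| 0.3 | 5.1% | 6.3% | 9.6% | 15.7% | 35.8% |
| 0.5 | 5.0% | 8.3% | 17.8% | 35.3% | 77.0% |
| 0.7 | 5.0% | 11.3% | 31.6% | 60.8% | 96.9% |

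Hand check of the middle cell: the mean simulated correlation is -0.094, so t ≈ -0.094 × √(119 / (1 - 0.094²)) ≈ -1.03. Against a critical value of 1.98, the chance of rejection is about P(Z > 0.95) ≈ 17%, in line with 17.8%. Positive values of q give the same rates by symmetry, with the slope reversed.

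**With baseline CES-D as a covariate.** The rate is 4.6% to 5.6% in every cell, and the mean partial correlation is about zero.

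**With a change score instead.** This does not repair the model. The expected correlation becomes -q × √((1 - ρ)/2). At ρ = 0.5 and q = -0.3 that is 0.3 × 0.5 = +0.15 (simulated +0.142, rejection 34.9%), so the bias changes sign.

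**With a second confounder.** Suppose another factor, such as motivation, raises attendance and lowers follow-up CES-D with paths of 0.2, 0.3 or 0.4, alongside a baseline-attendance path of -0.2 and a baseline-outcome path of 0.5. The unadjusted model then rejects in 31.5%, 52.3% and 79.2% of replicates. With baseline CES-D alone added it still rejects in 7.7%, 19.1% and 50.7%.

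**The case against.** The strongest reply is that the absence of covariates is read from silence. The article gives this analysis one sentence, lists no covariates for its primary model either, and may leave such detail to a fuller document. That is fair as far as it goes, and a fuller document could contain the adjustment. But the sentence does name a population, an outcome, a regressor, a test level and a dose-response purpose. The neighbouring predictor analysis does spell out its outcome, main effects and interactions. Followed as published, the model is open to confounding, and the limitations in the Discussion do not mention self-selected attendance.

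A second reply is that the analysis is exploratory and dose-response is not among the stated aims. That stands, and it limits the importance of the point.

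Some stronger readings are tempting but not supported:

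- A reader might infer that the model will show a dose effect whenever less depressed participants attend more, or that a spurious result is likely. At -0.2 and 0.5, about 82% of replicates show no significant slope, and no section says which participants attend more.
- A reader might infer that baseline CES-D and motivation are collected but never used. They are used elsewhere in Statistical analyses: baseline CES-D in the effect sizes and change measures, motivation in the predictor analysis. They are only unnamed in this model.
- A reader might infer that non-attenders will be the t1 non-responders, with mostly imputed outcomes. Invitations, reminders and payments do not depend on attendance, and the article draws no such link.
- Leaving out the waiting list is not an error in itself, since the waiting-list group has no sessions to vary before t1.

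**Conclusion.** The point holds as a limited one. The within-arm slope, as specified, is biased if baseline severity or motivation is related to both attendance and later CES-D, and its direction cannot be settled from the article. The inflation may be negligible or very large depending on correlations that only the trial data can supply, so no single cell of the table should be taken as a forecast. Adjustment for baseline CES-D removes the part due to severity and does not by itself make the slope causal. The table also assumes t1, complete outcomes and independent observations. The sample size and the randomised comparison are not affected.

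**What to change.** Reword the dose-response sentence in Statistical analyses to:

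- name t1 as the time point of the outcome;
- include baseline CES-D as a covariate, not through a change score;
- include the baseline motivation subscales (NML-P);
- apply the cluster-robust standard errors already specified for the t1 comparison, clustered by course group;
- describe the result as an association between attendance and symptoms, with a note that residual confounding can remain.

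All the variables are already collected, so the cost is a little more analysis work and a more cautious conclusion.

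An instrumental-variable estimate using allocation is optional. With the waiting list at zero sessions, it is essentially the between-arm difference divided by mean sessions attended. It therefore says little about whether more sessions do better than fewer, and it assumes that allocation acts only through attendance.

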## Discussion

The study described here is a randomised controlled trial in which young people aged 16 to 25 with depressive symptoms will take the GOJD (Master Your Mood) online group course; the outcomes will be compared to those of a waiting list control group. The primary aim is to assess the effectiveness of the online course in terms of severity of depressive symptoms. Secondary aims are to study effect maintenance and to identify predictors of positive outcomes.

Internet-based interventions are known to be effective in addressing depression. By virtue of their anonymity and the reduced need for contact between participants and professionals, they hold promise to reach many individuals who need them. In the field of web-based interventions for depression, studies with young people are still scarce, as are studies on online group courses. This trial should add to the body of knowledge on the effectiveness of such interventions. We shall now discuss some methodological issues in the current trial.

A strong feature of the current trial is that the recruitment and screening of participants and the inclusion and exclusion criteria are similar to the usual procedures in mental health agencies. This should enhance the external validity of the results. The main differences between the study and routine care are the randomisation and the informed consent required for the study. In addition, in routine care, participants with CES-D scores higher than 45 may be allowed to participate in the course, if only in exceptional cases in pressing circumstances and under specific conditions.

One limitation of the study concerns the impossibility of comparing the GOJD outcomes with those of the waitlisted group at the six-month follow-up, since the latter will receive access to the course three months after baseline. This means that the longer-term effectiveness of the course cannot be assessed in this study. We will, however, study effect preservation at six months in the GOJD group. Another study limitation is that the blinding of participants to experimental conditions is not feasible, because of the behavioural nature of the intervention.

A point of discussion is how far results can be generalised. To minimise selection bias, we will recruit participants via a broad range of channels: advertising in local and national newspapers, website banners, and leaflets in doctors' offices, mental health agencies and schools. Each participant's recruitment channel will be recorded; the distribution of the various channels will determine the degree of generalisability. Selection bias could also arise from personality traits of people attracted to a group intervention; these might differ from the traits of those who prefer individual therapy or no help at all.

A final limitation is that study participants will not be diagnosed. They will be selected on the basis of self-rated instruments, together with a diagnostic interview (MINI-Plus) in the chatroom, which is used as a screener to exclude applicants with suicidal tendencies. This means that the current study will be difficult to compare with studies in which participants have been diagnosed. The results will therefore not be generalisable to people with a DSM diagnosis of depression.
